##### Endothelial Independent Dilation

EID will be assessed in response to sublingual nitroglycerin to assess smooth muscle sensitivity to NO. EID will be determined by measuring brachial artery dilation for 8 min after sublingual nitroglycerin administration (0.4 mg) using high-resolution ultrasonography, as described above. Absolute change and percent change in arterial diameter will be used for analysis. EID will be performed at baseline, after the 24-week training period, and at 4- and 12-weeks post-intervention.

##### Arterial Stiffness

Arterial stiffness will be assessed *via* carotid-femoral pulse wave velocity (PWV_CF_) using a transcutaneous tonometer (SPT-301 ADInstruments, Colorado Springs, CO) placed sequentially in position at the carotid and femoral arteries, with simultaneous electrocardiograph (ECG) recording (59). PWV_CF_ will be calculated as mean distance/transit time. Transit time will be determined as the time between the ECG R-wave and carotid pulse subtracted from the time between the ECG R-wave and femoral pulse. Thirty consecutive pulse waves from each arterial site will be analyzed and averaged. PWV_CF_ will be calculated from difference in carotid-sternal and femoral-sternal distance (m) divided by difference in transit time (s). PWV_CF_ will be assessed at baseline, after the 24-week training period, and at 4- and 12-weeks post-intervention.

##### Influence of Circulating Factors on Nitric Oxide and Reactive Oxygen Species Production

Using blood drawn from experimental groups we will determine if IMST improves endothelial function *via* changes in circulating factors that increase endothelial cell NO production and/or reduce endothelial ROS production in cultured human umbilical vein endothelial cells (HUVECs) (American Type Culture Collection). We will expose HUVECs *ex vivo*, to media conditioned with serum drawn from participants in each group as described previously (52). After 2–4 passages, HUVECs will be plated in 96-well culture plates and incubated for 24 h at 37°C and 5% CO_2_ in basal media supplemented with 10% subject serum obtain before and after 24 weeks of low-resistance or high-resistance IMST. After incubation, cells will be co-incubated with fluorescent probes DAR-4M AM to detect NO production, and CellROX Deep Red to detect ROS production. Cells imaged with DAR-4M AM will be imaged 5 min after the addition of 200 μmol/L of acetylcholine to the cell culture media to stimulate NO production. Analysis will be done with Image J (National Institutes of Health). Data will be expressed as a fold change in NO/ROS production relative to the baseline timepoint.

##### Casual Diastolic Blood Pressure

Casual (resting) measures of DBP will be measured according to ACC/AHA guidelines (28). Measures will be made in triplicate over the brachial artery of the non-dominant arm after 5 min of quiet rest, with 1 min of recovery between each measure. Subjects will be seated quietly with their back supported, feet flat on the floor, and arm at heart level. DBP will be measured with an automated oscillometric sphygmomanometer (SunTech CT40, SunTech Medical), validated according to British Hypertension Society, International Protocol, and Association of Medical Instrumentation standards. Mean DBP will be calculated as the average of the three pressures, and will be recorded at baseline, weekly throughout the intervention, post intervention, and at 4- and 12-weeks post-intervention.

##### Twenty-Four-Hour Ambulatory Diastolic Blood Pressure

Twenty-four-hour DBP will be assessed with 24-h ambulatory non-invasive BP monitoring, as described above. Ambulatory DBP will be averaged over the entire 24-h period at baseline, post intervention, and at follow-up 4- and 12-weeks after cessation of the intervention.

##### Daytime and Nighttime Ambulatory Diastolic Blood Pressure

Ambulatory DBP data will be broken into daytime (16 h) and nighttime (8 h) segments according to subjects' individual sleep-wake cycles. Mean DBP (mmHg) will be calculated for the daytime and nighttime periods to evaluate circadian DBP profile at baseline, after the 24-week training period, and at 4- and 12-weeks post-intervention.

##### Six-Minute Walk Distance

A six-minute walk test will be performed in a 30-m hallway with cones to mark the ends of the track. The subject will be instructed to walk as quickly as they can, without running, for 6 min. They will start at the first cone and walk down the hallway, rounding the second cone, and returning up the hallway toward the first cone. They will continue to walk up and down the hallway, completing as many laps as possible in 6 min. Subjects will be told how much time is remaining every minute of the test, and with 30 and 10 s remaining, and encouraged to walk as quickly as possible each time. Distance covered in 6 min will be recorded at baseline, after the 24-week training period, and at 4- and 12-weeks post-intervention.

##### NIH Toolbox—Cognitive Domain

Subjects will complete the 7 cognitive domain assessments from the NIH Toolbox for the Assessment of Neurological and Behavioral Function (60). These tests include: (1) flanker inhibitory control and attention test; (2) dimensional change card sort test; (3) list sorting working memory test; (4) picture sequence memory test; (5) oral reading recognition test; (6) picture vocabulary test; and (7) pattern comparison processing speed test. All tests will be performed on an iPad (Apple Inc, Cupertino, CA, USA) with an investigator presenting task instructions and monitoring compliance, as recommended by the American Academy of Neurology (60). Scores will be recorded at baseline after the 24-week training period, and at 12-weeks post-intervention.

##### Maximal Inspiratory Pressure

Maximal inspiratory pressure (PI_max_) will be assessed by having subjects generate 3 maximal inspiratory efforts against near-infinite resistance measured at the mouth with a POWERbreathe™ KH2 trainer (POWERbreathe™ KH2, POWERbreathe International Ltd., Warwickshire, ENG). The KH2 includes computer software (Breathe-Link Medic, POWERbreathe International Ltd., Warwickshire, ENG) that gives live feedback and can assess PI_max_ and peak inspiratory flow. If there is >10% difference between efforts, subjects will perform up to 3 more efforts to ensure PI_max_ is achieved. The average of the 3 greatest pressures will be used for analysis, and will be assessed at the first exercise session, after the 24-week training period, and at 4- and 12-weeks post-intervention.

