**Arterial assessments**								
PWV_CF_	X						X		X
PWV_CF_ with NS		X						X		X
FMD_BA_	X						X		X
FMD_BA_ with NS		X						X		X
FMD_BA_ with vitamin C		X						X		X
EID with SL NTG		X						X		X
**Randomization**		X								

*6MW, six-minute walk; CHAMPS, Community Health Activities Model Program for Seniors physical activity questionnaire; BP, blood pressure; EID, endothelium-independent dilation; ESS, Epworth Sleepiness Scale; F4, first follow-up at 4 weeks; F12, second follow-up at 12 weeks; FMD_BA_, brachial artery flow-mediated dilation; HSAT, home sleep apnea testing; Hx, history; NS, normal saline infusion; NTG, nitroglycerin; PI_max_, maximal inspiratory pressure; PNE, plasma norepinephrine; PSQI, Pittsburgh Sleep Quality Index; PWV_CF_, carotid-femoral pulse wave velocity; SL, sublingual; V, visit. ^†^Surveys completed at home: CHAMPS, PSQI, ESS*.

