### Baseline Assessments

Eligible participants who are enrolled into the study will undergo the Outcome Assessments and Internal Control Assessments, found in Table 3, within a period of 14 days. Subjects will be asked to maintain their behavior throughout the study, and we will account for unreported changes with the Internal Control Assessments. Protocols for these assessments can be found in the Supplementary Material.

**Table 3 T3:** Outcome assessments and internal controls.

**Outcome assessments**	**Internal controls**
• Casual BP • 24-h BP monitoring • Blood draw • EDD *via* FMD_BA_ (with and without systemic saline and vitamin C infusion) • EID *via* sublingual nitroglycerin • Arterial stiffness *via* PWV_CF_ • 6MW • NIH Toolbox—cognitive domain • PI_max_ • Resting heart rate • Home sleep apnea testing • Grip strength • MSNA (subset of participants)	• Anthropometrics • Surveys • PSQI • ESS • CHAMPS • Actigraphy • Spirometry • Sleep and physical activity diaries

*Outcome Assessments include primary, secondary, and other outcomes of interest in the CHART study. Internal Controls will be completed to determine consistency of behavior throughout the study and to account for unreported changes. See Supplementary Material for protocols related to Internal Controls. 6MW, six-minute walk distance; BP, blood pressure; CHAMPS, Community Healthy Activities Model Program for Seniors physical activity questionnaire; EDD, endothelial-dependent dilation; EID, endothelial independent dilation; ESS, Epworth Sleepiness Scale; FMD_BA_, brachial artery flow-mediated dilation; PI_max_, maximal inspiratory pressure; PSQI, Pittsburgh Sleep Quality Index; PWV_CF_, carotid-femoral pulse wave velocity*.

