### Intervention

Following baseline assessments, participants will begin the training intervention. All training will be performed on the POWERbreathe™ K3 trainer (POWERbreathe™ K3, POWERbreathe International Ltd., Warwickshire, ENG), a handheld pressure-threshold device that can: (1) be pre-programmed to provide the appropriate resistance to inspiration, and (2) record data from all training sessions. Each participant will be provided their own device on which to perform their prescribed exercise at home, 5 days/week for 24 weeks, and will receive verbal and written instruction on the training protocol and K3 operation from the unblinded Research Technician.

The Research Technician will supervise the subject's first training session to ensure proper technique and comprehension. In training weeks 1–3, participants will perform 5 training sessions per week; one training session will be supervised by the Research Technician in the CATS facility, and 4 training sessions will be performed unsupervised at home. In training weeks 4–24, participants will perform training sessions unsupervised at home returning to the CATS facility for supervised training sessions twice monthly. At each visit, the unblinded Research Technician will determine the participant's casual BP, collect sleep and activity logs, transfer saved training data from the K3 device, and record any changes in medications, diet, exercise, and/or health status since the previous visit. The participant will complete 3 PI_max_ efforts to establish the following weeks' training level. The new resistance will be set on the K3 using the *Manual* function to ensure that the target resistance remains the same until the next in-person visit. The participant then will perform one supervised training session at this new training level. Subjects will be contacted weekly *via* phone or email to encourage participants and aid in retention and adherence.

Subjects assigned to high-resistance IMST will train against a resistance set at 75% of their PI_max_. Subjects randomly assigned to low-resistance IMST will train against a resistance set at 15% of PI_max_. Subjects in both groups will perform 5 sets of 6 breaths, with 1 min rest between sets, for a total of 30 breaths per day (49). All exercise sessions will be recorded in the device memory card and participants will be required to complete a weekly training log.

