### Randomization, Blinding, and Treatment Allocation

Participants will be randomized after completing baseline assessments. Assignment to the training program will be by an unblinded Senior Research Professional. The study statistician will use a computer-generated randomization list for the study. Block randomization with block sizes of 2, 4, and 6 will be used to randomize participants into two groups (high- vs. low-resistance IMST) in a 1:1 ratio. Randomization will be stratified by sex (M/F) and OSA disease severity (moderate/severe). The randomization list will be stored in a .CSV file with the randomized group assignment hidden and only revealed by the Senior Research Professional at the time of randomization. Assignment to groups will be sequentially within strata.

Randomization will, on average, balance CPAP users (Yes/No) between the two arms within sex and severity strata however, the effect of treatment may differ depending on CPAP use. We will account for the potential effect of CPAP on outcomes, and possible interaction with treatment, by including CPAP and treatment-by-CPAP interaction effects in the mixed effects models. Based our pilot trials, we anticipate ~10–15% CPAP users in our study sample. The power to detect either a CPAP or a treatment-by-CPAP interaction, that is, our ability to tease out CPAP from IMST effects, will depend on the treatment-by-CPAP cell sample sizes and effect sizes.

Outcomes assessors and data analysts will be blinded to training group allocation. As both training programs have the potential to affect outcome measures, neither is considered a “placebo.” Subjects will be blinded to their allocation group.

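### The first PImax value is taken after randomisation, in a session supervised by the unblinded technician, although Table 3 lists PImax among the pre-randomisation baseline assessments

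*Protocol article*

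**What the plan says.** All references are to the protocol article.

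- **Maximal Inspiratory Pressure (Other Outcomes).** PImax "will be assessed at the first exercise session, after the 24-week training period, and at 4- and 12-weeks post-intervention". Participants make three maximal efforts on the KH2 device, whose software gives live feedback. If efforts differ by more than 10%, up to three more are made, and the three greatest are averaged.
- **Table 2, PImax row.** Both baseline cells are empty. The first mark is in week 1 of the exercise intervention, followed by the later training columns, post-intervention visit 1 and follow-up visit 1.
- **Table 2, randomisation row.** The only mark is at baseline visit 2.
- **Baseline Assessments and Table 3.** "Eligible participants who are enrolled into the study will undergo the Outcome Assessments and Internal Control Assessments, found in Table 3, within a period of" (the window given is 14 days). Table 3 lists PImax among the outcome assessments.
- **Randomization, Blinding, and Treatment Allocation.** "Participants will be randomized after completing baseline assessments". Outcome assessors and participants are said to be blinded.
- **Intervention.** "Following baseline assessments, participants will begin the training intervention". "The Research Technician will supervise the subject's first training session to ensure proper technique and comprehension". Participants "will receive verbal and written instruction on the training protocol and K3 operation from the unblinded Research Technician". At training visits three PImax efforts set the resistance, at 75% or 15% of PImax according to arm.
- **Statistical Analysis.** One approach serves all hypotheses: a repeated-measures mixed model, with arms compared on average change from baseline.

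**The concern.** Two parts of the article give incompatible times for the first PImax value, and staff cannot follow both. On the timing in the outcome definition and in Table 2, the only value that can serve as baseline is obtained after allocation, in a session run by someone who knows the arm.

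That matters more for PImax than for an automated reading. It is a voluntary maximal effort, and encouragement and the handling of repeat efforts can influence the result. Participant blinding does not remove that route, because it runs through the person conducting the session.

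If the baseline is affected differently in the two arms, the difference passes into the change from baseline. Randomisation does not protect a baseline collected after allocation. At stake is the between-arm comparison of change in PImax, and any statement about how far the two loads altered inspiratory muscle strength.

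**Working it through.** The article gives no sample size, effect size, standard deviation or power for PImax, so there is no stated figure to reproduce. The check is of the order of events, who is present, and how the value is used.

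**1. Order of events**

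| Step | Event | Source |
|---|---|---|
| 1 | Baseline visits 1 and 2, with no PImax marked | Table 2 |
| 2 | Randomisation, once baseline assessments are complete | Randomization section; Table 2, baseline visit 2 |
| 3 | First exercise session, within 14 days of the second baseline assessment | Study Location and Timeline; Intervention |
| 4 | First PImax value, at that session | Maximal Inspiratory Pressure; Table 2, week 1 |
| 5 | PImax at post-intervention and both follow-ups | Maximal Inspiratory Pressure; Table 2 |

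This order does not depend on how the table's columns were read. The prose alone places randomisation after the baseline assessments and PImax at the first exercise session. Nor can that session be counted as part of baseline: Table 2 gives baseline as days -14 to 0 and week 1 as days 1 to 7.

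**2. The conflicting statement.** Table 3 includes PImax, and the Baseline Assessments section has the Table 3 assessments done within the baseline period. That places a PImax measurement before step 2. Neighbouring outcomes in the same part of the article (six-minute walk, resting heart rate, grip strength) are defined with a baseline measurement. PImax is worded differently.

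**3. Who is present.** The first session is supervised by the Research Technician, whom the same section describes as unblinded. Resistance is a percentage of PImax that depends on the arm, so a PImax value and the allocation are both needed to set it. The article does not say who takes the outcome reading at that session, and it does not assign it to a blinded assessor.

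**4. How an arm-specific shift would act.** Let the mean baseline be displaced by d_H in the high-resistance arm and d_L in the low-resistance arm, with post-intervention values unaffected. The between-arm difference in change becomes

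(Post_H - B_H - d_H) - (Post_L - B_L - d_L) = [(Post_H - B_H) - (Post_L - B_L)] + (d_L - d_H).

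The bias is d_L - d_H. It is zero if coaching affects both arms equally and non-zero only if it differs by arm. The article contains nothing from which d_H or d_L could be estimated, so no magnitude is given.

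A comparison of post-intervention values alone does not contain d_H or d_L. The exposure therefore belongs to the change-from-baseline analysis, which is the one the Statistical Analysis section specifies.

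**The case against.** The case against giving this weight is substantial, and most of it stands.

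- **Importance.** PImax is one of many Other Outcomes. The abstract does not name it, and neither the primary hypothesis nor the other hypotheses concern it. Delivery of training is documented by device memory, training logs and session counts. A reader might infer that the trial's main conclusions are in doubt; nothing in the article supports that.
- **Operator.** A reader might infer that the technician is known to take the first reading. The text says only that the technician supervises the session. The inference is close, since the value is needed there to set the load, but it remains an inference.
- **Conditions.** A reader might infer that baseline and later values come from different procedures. The outcome definition sets one procedure for all time points, with the same device, efforts, repeat rule and averaging. The one supportable difference is a possible change of operator.
- **Mechanism and size.** Both arms need a true maximum, and the repeat rule and the averaging of the best three guard against weak effort in both. The article gives no reason to expect weaker coaching in one arm. The 10% repeat rule concerns spread among one person's efforts and says nothing about a systematic difference between arm means, so it cannot be used to size a bias.
- **Repair.** A reader might infer that the harm could not be undone. It could be avoided in analysis by comparing post-intervention values between arms.

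These points limit the concern without removing it. The sections still disagree on timing, and under the outcome definition and Table 2 the baseline is still obtained where allocation is known, for a measure that depends on effort.

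**Conclusion.** The point holds as a contradiction in timing together with an avoidable risk of bias. The outcome definition and Table 2 agree that the first PImax follows randomisation, in a session the unblinded technician supervises. The Baseline Assessments section with Table 3 puts PImax before randomisation. Because change from baseline is analysed, the first timing leaves the baseline open to influence by knowledge of the arm.

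The size is unknown and may be zero. The conclusion about bias assumes that the first-session value would serve as the outcome baseline, which is the only candidate under the outcome definition, and that the person conducting the efforts may know the arm. The conclusion about the contradiction needs neither assumption. The effect is confined to one of the Other Outcomes; casual systolic pressure, 24-hour systolic pressure and plasma norepinephrine are not touched. The change is worth making because it is cheap and specific, and Table 3 already implies it.

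**What to change.** Reconcile the Maximal Inspiratory Pressure section, the PImax row of Table 2, and the Baseline Assessments section with Table 3:

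1. Add a PImax measurement at baseline visit 1 or 2, before randomisation, under the procedure already in the outcome definition and by the assessor who takes the other baseline outcomes. Visit 1 would mirror the post-intervention and follow-up schedule, where PImax is marked at visit 1.
2. State in the outcome definition that this value is the PImax baseline for analysis.
3. State that PImax values obtained at training visits are used only to set the training load and are not outcome data.

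In Table 2 this adds a mark at a baseline visit. The training-visit marks stay, because the load still has to be set from them, and the training itself does not change. The cost is a few extra minutes of maximal efforts at one visit that already takes place, plus short edits to the text. The device is the one already named, and the work fits the assessor's existing visit.

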##### Resting Heart Rate

Resting heart rate will be measured simultaneously with blood pressure using the same automated oscillometric sphygmomanometer as is used for blood pressure assessments (SunTech CT40, SunTech Medical). As with blood pressure, heart rate will be defined as the average of the three readings at baseline, and will be performed at baseline, after the 24-week training period, and at 4- and 12-weeks post-intervention.

##### Home Sleep Apnea Testing

Severity of obstructive sleep apnea (i.e., AHI) will be assessed with a Nox T3s Home Sleep Apnea Testing diagnostic device (Nox T3s, Nox Medical, Reykjavik, IS), a Type III polygraph with actigraphy. Subjects will be instructed on the use and fitting of the device. They will be instructed to turn on the device immediately prior to going to bed and to turn it off upon waking. Subjects with an AHI < 15 will be excluded from the study. Outcomes include total sleep time, apneas/hour, hypopneas/hour, average O_2_ saturation (SpO_2_), minimum SpO_2_, duration of SpO_2_ < 90%, and duration of SpO_2_ < 85%. Home sleep apnea testing will be performed at baseline and after the 24-week training period, but not at 4- and 12-weeks post-intervention.

